## Materials and methods

### Objectives

The main objective of this study is to evaluate the effectiveness and feasibility of the StAB project (German: Start in Ausbildung und Beruf, [= Start in education and employment]), a supported employment and education intervention for mentally burdened adolescents and young adults. Based on the IPS approach, StAB aims at facilitating entry or re-integration to the general labor market or regular vocational training.

We assume that the intervention will result in an increased psychosocial participation and functioning of the participants (primary outcomes). At the same time, barriers and inhibiting living conditions are expected to decrease, so that quality of life, self-efficacy and other dimensions of the participants will improve. In terms of occupational parameters, we expect at least 40% of the participants to have completed education or vocational training or a specific preparatory internship, or to have returned to work or are employed at the primary labour market within two years after program enrolment. In addition, the effects of the intervention will be analyzed regarding further outcome variables, e.g. self-esteem, psychopathological symptoms or need for inpatient treatment.

The StAB project also aims to structurally change the local health and social care system. For this purpose, the implementation of a cross-sector competence network with relevant stakeholders and key informants from the fields of pediatric and adolescent medicine, child and youth work, education, vocational rehabilitation, and psychosocial support is planned.

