### Assessments

The baseline assessment is intended to acquire data on different participant characteristics by means of a study-specific questionnaire, e.g. demographics, educational status, employment history, work situation, utilization of (mental) health services, and expectations towards study participation. Furthermore, several standardized questionnaires (see below) will be handed out to participants for self-completion, but they can receive support or clarification from the research team member at any time if they want to. In addition, a brief screening test of cognitive functioning will also be performed. The whole assessment procedure is expected to take approximately 75 to 90 minutes. It will be carried out by experienced, trained and supervised research team members that can support participants that have questions regarding the questionnaires. In addition to the baseline assessment (t0), there will be a short interim assessment after one year (t1) and a final assessment at the end of the intervention after a maximum of two and a half years (t2). The t2 assessment is announced early and repeatedly, and its implementation is closely coordinated with participants to achieve high participation rates, even among potential dropouts.

Moreover, in addition to the study assessments we plan to include standardized process data from the IPS coaches to obtain information on frequency, amount, and type of support across the course of the StAB program. An overview of all variables, instruments and outcome measures utilized in the study is given in Table 1.

**Table 1 pone.0271803.t001:** Diagnostic instruments and assessment schedule (the full names of the instruments are given in the text, see Measures).

		STUDY PERIOD		
		T0 (baseline assessment)	T1 (short interim assessment)	T2 (final assessment)
**TIMEPOINT** (months)		0	12	24

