In addition to the aforementioned measurement instruments, we will collect data on **various participant characteristics** across the study period using study-specific and self-constructed questionnaires. Here, the main focus is on professional and educational development, utilization of psychosocial support services as well as participation in and satisfaction with the program. Moreover, we also plan to include standardized process data from the IPS coaching team to obtain information on frequency, amount, and type of support across the course of the program. Additionally, the subjectively perceived impact of the corona pandemic on the education and employment situation of the participants will be obtained. For this purpose, questions from a recent short survey on vocational perspectives for people with mental illness under corona conditions will be used [61].

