#### Data analyses

Before data analysis, the data set will be inspected with regard to inconsistencies and missing values. Missing data will be addressed by applying linear mixed models, if appropriate. We will perform a dropout analysis to check for differences between program completers and non-completers with regard to main demographic, psychosocial, and work-related variables. Besides descriptive baseline data analysis, we will primarily analyse changes in the main outcome measures from baseline to final assessment (after up to a maximum of 2.5 years). Theses analyses on the study outcome measures will be performed as intention-to-treat, supplemented by a “per-protocol”-analysis including all individuals who have completed the StAB program without dropping out. Of course, a repeated-measures approach is used if indicated. Program effects on outcome measures will be explored by taking into account relevant covariates, like key baseline variables, changes in some measures within the first year (see above) or program specific variations, e.g. number and total duration of coaching sessions. Program feasibility and acceptance among the participating adolescents and young adults with mental health difficulties will be evaluated using process documentation data as well as subjective ratings in the final assessment.

The statistical analysis of the data will be done using the software package IBM SPSS Statistics Version 25 and the level of statistical significance will be set to p < .05.

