Nevertheless, the implementation and evaluation of the presented study is also associated with some challenges and limitations. For instance, we will face possible challenges with regard to the recruitment of the targeted group of people. Emerging adults with mental illnesses already face many difficulties to cope with a particularly vulnerable phase of life. It has been shown that they may not actively seek professional help themselves (see [73]) due to stigmatization and shame as well as a preference for self-reliance [74] and that they tend to disengage from ongoing intervention services by virtue of adverse vocational trends (e.g. [75]). Thus, accessibility to the program and reachability to these young people across the study period may be potentially difficult. We therefore expect a 30% dropout rate, in line with other IPS studies [76] and even slightly higher than comparable vocational programs for mentally burdened young adults [77].

Another challenge to both study initiation and implementation may be the ongoing (or re-emerging) restrictions due to the Corona pandemic. In addition to constraints on the conduct of research projects (e.g. [78]), the longer-term work-related perspectives and participation opportunities of people with mental illness seem to have been additionally worsened under Corona conditions [61]. Moreover, of course, many young individuals have reported being highly burdened by the pandemic [79] and experiencing more mental health problems [80].

A methodological limitation of the present study is the use of a single group pre-post design, because we will not be able to control for potential confounders. In order to have something similar to a control group, we will compare the data from participants of the IPS coaching with data of the federal average or data of standard labour market policy measures. Wherever possible, not only intra-group changes will be analysed, but also comparisons with published norms of the test procedures as well as results of other studies will be used. Nevertheless, a RCT study design should be a future approach.

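### Participants' own ratings of the programme enter the acceptance analysis only at the final assessment, so acceptance is likely to be overstated if leavers do not attend it

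*Protocol article*

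**What the plan says.** The Objectives section states: "The main objective of this study is to evaluate the effectiveness and feasibility of the StAB project". Acceptance is not named there. It appears beside feasibility in the Data analyses section, where both are to be "evaluated using process documentation data as well as subjective ratings in the final assessment".

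Four other places bear on the point.

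- **Measures, further measures and questions.** Participant characteristics are collected "across the study period using study-specific and self-constructed questionnaires", and one stated focus is "participation in and satisfaction with the program". The coaching records are described as "standardized process data from the IPS coaching team to obtain information on frequency, amount, and type of support across the course of the program".
- **Assessments and Table 1.** There are assessments at 0, 12 and 24 months, with the text allowing the last at up to two and a half years. The study-specific questionnaires are repeated partially at t1. Table 1 lists satisfaction with medical care among them but does not list satisfaction with the programme. The conduct of t2 is to be "closely coordinated with participants to achieve high participation rates, even among potential dropouts".
- **Sample size and Discussion.** The calculation raises 52 to 75 for dropout of at least 30%, and the Discussion repeats: "We therefore expect a 30% dropout rate, in line with other IPS studies".
- **Data analyses.** A dropout analysis will compare completers with non-completers on demographic, psychosocial and work-related variables.

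**The concern.** Leaving a voluntary programme can itself be a sign that it did not suit the person. If opinion is taken only from those who come to the final assessment, the people most likely to hold a poor opinion are the most likely to be missing from it.

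The other planned sources do not fill this gap. As described, the coaching records hold how often, how much and what kind of support was given, not what the participant thought of it or why they left. The dropout analysis shows who left, but neither opinion nor reason is among its variables. Linear mixed models, which the plan names for missing data, cannot help if the rating is used at t2 alone, because a non-attender then has no earlier rating for the model to use.

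The study is single-arm and its main objective includes feasibility. A figure for acceptance that is too favourable would feed directly into that conclusion. The Measures section suggests that earlier satisfaction data may exist, in which case the analysis rule leaves them unused.

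**Working it through.** **1. The plan's own figures.** Inputs from the Sample size section: paired t-test, d = 0.4, alpha 0.05, power 0.80, dropout 30%. With a two-sided test (sidedness is not stated) the noncentral t distribution gives n = 52 with power 0.808; a one-sided test would give 41. Inflation: 52 / 0.70 = 74.3, rounded up to 75. Both stated figures reproduce.

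**2. What the inflation implies for t2.** A paired comparison needs a t2 value. Enlarging 52 to 75 for dropout therefore allows for up to 75 − 52 = 23 people without one. Acceptance ratings taken at t2 would be missing for the same people.

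**3. Width of the bounds.** Let N = 75 be enrolled, m unrated and s satisfied among those rated. Acceptance over all enrolled lies between s/N (no unrated person accepts) and (s + m)/N (all do). The width is m/N, whatever s is.

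| Share of the 23 leavers rated at t2 | Unrated m | Width m/75 |
|---|---|---|
| none | 23 | 31 points |
| one quarter | 17.25 | 23 points |
| one half | 11.5 | 15 points (16 if m is rounded up to 12) |
| three quarters | 5.75 | 8 points |

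**4. Example.** The document gives no acceptance rate, so one is assumed: 44 of 52 raters satisfied, 44/52 = 85%. With no leaver rated, the lower bound is 44/75 = 59% and the upper bound is (44 + 23)/75 = 67/75 = 89%. Other assumed responder rates move the interval but keep its width: 70% gives 49% to 79%, 80% gives 55% to 86%, and 90% gives 62% to 93%.

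**5. Direction.** With responder rate pR and leavers' rate pL, the responder rate exceeds the rate over all enrolled by (m/N) × (pR − pL). With m = 23 and pR = 80% (assumed):

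- pL = 50%: (52 × 0.80 + 23 × 0.50)/75 = 71%, an overstatement of 9 points.
- pL = 20%: (52 × 0.80 + 23 × 0.20)/75 = 62%, an overstatement of 18 points.
- pL = 80%: no bias.

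The bias is upward only if leavers are less satisfied than stayers. That is plausible for a voluntary programme, but it is an assumption.

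**The case against.** The case for leaving the plan as it is has real weight.

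- A reader might infer that acceptance rests on the final ratings alone. It does not: the same sentence names process documentation, which covers leavers up to the time they leave and can show contact falling away. This stands, but those records as described contain no opinion.
- A reader might infer that acceptance is half of the main objective. The Objectives section pairs effectiveness with feasibility and does not mention acceptance, which is only evaluated alongside feasibility.
- A reader might infer that leavers are largely left out. The documents do not support that. The Assessments section seeks t2 participation even from potential dropouts, and the outcome analysis is intention-to-treat, so leaving the coaching does not by design end follow-up. What remains is that this is an aim, while the sample size still allows for at least 30% loss.
- The reasons for leaving are not given. Some participants may leave because they found work or moved, and may rate the programme well. This is why both bounds are shown.
- A journal article condenses. The timing of single items and any exit contact may be set out in the full protocol or analysis plan, and the partial repeat at t1 may already include programme satisfaction. That limits the point to what the article itself fixes: a rule that takes subjective ratings from the final assessment, beside a statement that satisfaction belongs to data collected over the study period.

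**Conclusion.** The narrow point holds, as a cheap improvement and not as a flaw in the design. The article's rule draws participants' own view of the programme from t2 alone, does not say how the satisfaction data described under Measures enter the analysis, and allows for up to about 23 of 75 people without a t2 value. Leavers who do not attend would be missing from the acceptance ratings, and the result would then probably be too favourable.

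The size cannot be fixed from the document, because t2 attendance among leavers is not stated. It ranges from about 31 percentage points of uncertainty if no leaver is rated, through 15 to 16 if half are, to about 8 if three quarters are. These widths assume 75 enrolled and 23 leavers; every level of acceptance used above is an assumption, and so is the upward direction. It would go too far to say that acceptance is judged from final ratings only or that those who leave are largely excluded.

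**What to change.** Bring the Measures and Data analyses sections into line:

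1. Include the programme satisfaction items in the t1 assessment, and show them in Table 1.
2. State that the acceptance analysis uses each participant's last available rating.
3. Report acceptance with all enrolled as denominator, counting unrated leavers as not accepting (a lower bound), beside the rate among responders, and give the number rated.
4. Optionally, record the reason for leaving and a brief rating when a participant leaves. This would also reach those who go before t1.

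The cost is a few more items at t1, a short contact at exit if that option is taken, and a less favourable stated acceptance figure. The sample size and the primary analysis are unaffected. Opinions and reasons not recorded near the time of leaving are hard to recover later.

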#### Research ethics and standards

The study will be performed according to the “Guidelines for Safeguarding Good Research Practice” by German Research Foundation (DFG) [62], the Declaration of Helsinki [63] and in compliance with the relevant dataprotection regulations. The trial was approved by the Ethics Committee of the Medical Association of Westphalia-Lippe and the University of Münster on 02.03.2022 (2022-037-f-S), which had no ethical or legal concerns about conducting the study. Moreover, the present study was registered at the German Clinical Trials Register (DRKS00027576) and will be updated there in case of modifications and adjustments.

#### Ethics approval and consent to participate

Ethical approval for this study is granted by the Ethics Committee of the Medical Association of Westphalia-Lippe and the Westphalian Wilhelms University Münster (2022-037-f-S). Before participating in the study, all participants will read an information statement and give informed consent. For participants who have not yet reached legal age, an informed consent from a legal guardian is needed. Any modifications of the trial protocol will be communicated to the Ethics Committee.

## Discussion

International research has clearly highlighted the importance of work for the self-development, social engagement and recovery of young adults with mental health problems [8, 64–66]. However, many adolescents and young adults experience barriers along their educational and work pathways that lead not only to unsteady and inconsistent employment trajectories but also unfavourable health and social outcomes [10, 67, 68]. Long-term studies have demonstrated that psychiatric disorders between the ages of 18 and 25 were associated with decreasing likelihood of paid employment, lower full-time employment; fewer hours worked per week, and increased rates of welfare dependence at age 30 [69, 70]. Moreover, young people with (severe) mental disorders are less likely than any other disability group to be included in, or to benefit from, regular employment programmes [71]. The very latest "Third Participation Report of the Federal Government on the Living Conditions of People with Impairments" also shows that in Germany, people with severe mental or psychological problems are particularly often affected by unemployment and severe problems with participation in working life [72].

Performing the StAB program we intend to take up the call for a wider dissemination of individualized supported education and employment for young individuals with mental health problems [67, 71]. The StAB program includes low-threshold inclusion criteria for adolescents and young adults with a wide range of psychiatric diagnoses, offers long-term coaching support, accompanying school attendance, training or the start of an employment; operates in collaboration and coordination with the regular support system; features the option for an additional flexible “individual budget” for participant-related integration service, and additionally aims to establish sustainable network structures with relevant actors and institutions from the social and health care system.

Nevertheless, the implementation and evaluation of the presented study is also associated with some challenges and limitations. For instance, we will face possible challenges with regard to the recruitment of the targeted group of people. Emerging adults with mental illnesses already face many difficulties to cope with a particularly vulnerable phase of life. It has been shown that they may not actively seek professional help themselves (see [73]) due to stigmatization and shame as well as a preference for self-reliance [74] and that they tend to disengage from ongoing intervention services by virtue of adverse vocational trends (e.g. [75]). Thus, accessibility to the program and reachability to these young people across the study period may be potentially difficult. We therefore expect a 30% dropout rate, in line with other IPS studies [76] and even slightly higher than comparable vocational programs for mentally burdened young adults [77].

Another challenge to both study initiation and implementation may be the ongoing (or re-emerging) restrictions due to the Corona pandemic. In addition to constraints on the conduct of research projects (e.g. [78]), the longer-term work-related perspectives and participation opportunities of people with mental illness seem to have been additionally worsened under Corona conditions [61]. Moreover, of course, many young individuals have reported being highly burdened by the pandemic [79] and experiencing more mental health problems [80].

A methodological limitation of the present study is the use of a single group pre-post design, because we will not be able to control for potential confounders. In order to have something similar to a control group, we will compare the data from participants of the IPS coaching with data of the federal average or data of standard labour market policy measures. Wherever possible, not only intra-group changes will be analysed, but also comparisons with published norms of the test procedures as well as results of other studies will be used. Nevertheless, a RCT study design should be a future approach.

In sum, the presented StAB program will contribute to the wider dissemination and implementation of Supported Employment and Education for mentally ill adolescents. More specifically, it is intended to gain improved knowledge on the application of individualized placement and support in a sample of young people with different mental health problems in Germany. Beyond improving the young people’s participation in education or working life, and consequently their career prospects, StAB should also lead to positive changes in non-work-related characteristics, such as the adolescents’ psychosocial functioning, quality of life or self-efficacy.
